### 10.3.3 Secondary outcome analysis

The analysis of the following secondary outcomes will be presented as the estimated difference and 95% confidence interval between groups using a t-method from baseline to 48 and 96 weeks.

The mean change in ELF score

Mean change in the Fibroscan stiffness

Mean change in Fibroscan CAP score

Mean change in fasting lipids (HDL:cholesterol ratio, HDL, LDL, TG), ALT, fasting glucose, HbA1c, in the maraviroc and non-maraviroc groups

Mean change in the BMI, waist circumference and weight

Mean change in the CD4 count

Mean scores for the CLDQ:NAFLD , SF-36 and WAIP:SAH questionnaires

Differences in the following measures from baseline to 48 and 96 weeks will be presented exact 95% binomial confidence intervals:

% with HIV viral load not detected (48 and 96 weeks)

% with CT liver:spleen attenuation ratio <1.0 (96 weeks only)

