## Omega 3 fatty acids

Stratification will be undertaken to balance the treatment groups on important prognostic factors (ie to prevent confounding) given that high BMI [2] and concurrent administration of PIs [1] may be associated with faster fibrosis progression in some studies. Statin use has conversely been associated with relative protection from hepatic fibrosis progression in some NAFLD studies [22]. Diabetes mellitus has been associated with faster hepatic fibrosis progression in several studies [2].

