### **7.3 The randomisation scheme**

After written informed consent has been received and eligibility established, subjects will be randomised 1:1 into the maraviroc and non-maraviroc groups (Groups A and B respectively) at the baseline visit (day 1). In addition, there will be stratification according to (1) current exposure or past history of  $\geq 6$  months exposure to protease inhibitor (PI)-containing antiretroviral therapy versus no current exposure and less than 6 months past exposure to PI-containing therapy and (2) BMI  $\geq 25$  versus  $< 25$  and (3) current exposure to a lipid-lowering agent and (4) being diabetic type 1 or 2 vs non-diabetic.

The rationale for this stratification is to attempt to reduce the potential for imbalance in factors considered a priori to be prognostic of ELF. Elevated BMI may be associated with faster progression of hepatic fibrosis in NAFLD patients. In addition, exposure to PI-containing therapy has in some studies been associated with accelerated fibrosis progression [1]. In other studies, lipid-lower therapies may reduce fibrosis progression [22]. Finally, diabetes mellitus has been identified as one of the strongest predictors of fibrosis progression in NAFLD patients [2].

The web-based Sealed Envelope™ system will be used to allocate individuals randomly to the maraviroc or non-maraviroc groups. The statistician will provide the randomisation list. The HEPMARc Randomisation Guide should be followed by the study team.

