## **10 STATISTICS AND DATA ANALYSIS**

### **10.1 Sample size calculation**

This is a pilot study to evaluate the feasibility and potential efficacy of addition of maraviroc to optimised background combination antiretroviral therapy and therefore no formal sample size calculation has been conducted. Results may be used to estimate the variability of the treatment effect of MVC on the ELF score which in turn may inform the sample size calculation for a larger placebo-controlled RCT.

In a previous biopsy study, a unit increase of 1 in the ELF score was associated with a 2.5-fold increased risk of a liver-related event (adjusted for age and stage of fibrosis) and therefore a unit increase of 1 is deemed to represent a clinically important entity [24]. Assuming the SD of the ELF score is 1.12, with 20 patients in each group for the analysis, a difference in ELF of 1 point can be estimated with a 95% confidence interval from 0.6 to 1.4. Assuming an attrition rate of 33%, a target of 30 individuals will be recruited per group [23].

A t-method will be used to estimate the difference in ELF scores, together with 95% confidence intervals, between the two groups. P-values will not be presented.

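### Sections 10.1 and 10.3.3 fix an unadjusted t-method, leaving out the stratification factors and not adjusting for baseline; a linear model would give a modest gain in precision

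*Protocol*

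**What the plan says.** Section 10.3.3 gives one method for all continuous secondary outcomes: the "estimated difference and 95% confidence interval between groups using a t-method from baseline to 48 and 96 weeks". For ELF the listed quantity is "The mean change in ELF score". Fibroscan stiffness, CAP, lipids, ALT, glucose, HbA1c, BMI, waist, weight and CD4 are likewise listed as mean changes. The questionnaires are listed differently: "Mean scores for the CLDQ:NAFLD , SF-36" and WPAI.

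Section 10.1 says of ELF: "A t-method will be used to estimate the difference in ELF scores, together with 95% confidence intervals, between the two groups". It speaks of scores and not of change, and adds that no P-values will be given.

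On the design side, Section 7.3 states that "subjects will be randomised 1:1 into the maraviroc and non-maraviroc groups", stratified on protease-inhibitor exposure, BMI at or above 25, lipid-lowering therapy and diabetes. The reason given is to "reduce the potential for imbalance in factors considered a priori to be prognostic of ELF". Section 4 says the same: "Stratification will be undertaken to balance the treatment groups on important prognostic factors".

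Neither Section 10.1 nor Section 10.3.3, nor any other part of the protocol, names a covariate or a stratified analysis.

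**The concern.** Three features of the stated analysis do not fit the design.

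1. The stratification factors are used to allocate and then dropped. If they predict the outcome, balancing them reduces the true variability of the treatment difference, but an unadjusted t interval does not credit that reduction.
2. A change score fixes the slope on baseline at 1. A linear model estimates the slope and in large samples is never less precise.
3. The analysed quantity is not the same throughout. Section 10.1 can be read as comparing follow-up ELF scores, while Section 10.3.3 compares changes. The questionnaires are listed as mean scores although Table 1 collects them at baseline.

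At stake is the precision of the ELF estimate with about 20 analysed per group, and the form of the variability estimate that Section 10.1 says may inform a larger trial.

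**Working it through.** **Inputs.** From Section 10.1: SD of ELF 1.12, 20 analysed per group, a 1-point difference, a stated 95% interval of 0.6 to 1.4. The correlation r between baseline and follow-up ELF is not in the protocol; it is assumed and shown as a range.

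**The plan's own figure.** Standard error = 1.12 × √(2/20) = 0.354. Half-width = t(0.975, 38) × 0.354 = 2.024 × 0.354 = 0.717, so the interval would be 0.28 to 1.72. The stated half-width of 0.4 does not follow from SD 1.12 and 20 per group. It would follow for change scores if r were about 0.84, but no such assumption is stated. That discrepancy is a separate matter; the calculations below use the stated SD and n.

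**Formulas**, with N = 40 analysed:
- Follow-up score, t-method: t(38) × 0.354
- Change score, t-method: t(38) × 0.354 × √(2(1 − r))
- Linear model on baseline only: t(37) × 0.354 × √(1 − r²) × √(1 + 1/36)
- Linear model on baseline plus four factors that explain nothing further: t(33) × 0.354 × √(1 − r²) × √(1 + 5/32)

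The last term in each linear-model line is the expected variance inflation from p covariates, 1 + p/(N − p − 3).

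**Example, r = 0.7.** Change score: 0.717 × √0.6 = 0.555. Baseline only: 2.026 × 0.354 × 0.714 × 1.014 = 0.520. Five covariates: 2.035 × 0.354 × 0.714 × 1.075 = 0.553.

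| r (assumed) | Follow-up score | Change score | Baseline only | Baseline + four factors, none predictive |
|---|---|---|---|---|
| 0.3 | 0.717 | 0.848 | 0.694 | 0.739 |
| 0.5 | 0.717 | 0.717 | 0.630 | 0.671 |
| 0.7 | 0.717 | 0.555 | 0.520 | 0.553 |
| 0.8 | 0.717 | 0.453 | 0.437 | 0.465 |
| 0.9 | 0.717 | 0.321 | 0.317 | 0.338 |

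**What the table shows.**
- Baseline adjustment narrows the change-score interval by about 12% at r = 0.5, 6% at 0.7, 3–4% at 0.8 and 1% at 0.9. The large-sample variance ratio is (1 + r)/2: 0.75, 0.85, 0.90 and 0.95.
- The wording difference matters. Follow-up scores and change scores give the same half-width only at r = 0.5.
- The four factors have a cost. Relative to baseline only, they widen the interval by a factor of 1.065 if they predict nothing. They recover this once they explain 1 − 1/1.065² ≈ 12% of the residual variance. To match the change score they need less: about 5% at r = 0.8 (1 − (0.453/0.465)²) and 10% at r = 0.9 (1 − (0.321/0.338)²).

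**Simulation check** (3,000 runs per setting). At r = 0.7 the five-covariate half-width averaged 0.548, 0.521, 0.491 and 0.458 when the factors explained 0, 10, 20 and 30% of the residual variance, against 0.516 for baseline only and 0.55 for the change score. Coverage stayed close to 95% throughout. The factors were drawn at random and not balanced by stratified allocation, so the cost shown is an upper guide.

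**The case against.** Much can be said for the plan as written. Randomisation makes the unadjusted comparison valid before attrition. The outcomes are secondary, in a feasibility pilot with no P-values and no decision rule resting on ELF. The protocol hedges on how prognostic the factors are in the published studies. With 40 analysed, five covariates are not free: if the factors explain nothing beyond baseline, the full model gains little at r = 0.7 and is slightly wider than the t-method from r = 0.8 upwards. All of that stands and limits the size of the point. Covariates are often specified in an SAP, but here the protocol itself names the method, so an SAP that adjusted would depart from it.

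Four stronger readings are tempting but not supported:
- *The plan ignores baseline.* For the change outcomes baseline is subtracted. The description fits only the questionnaire mean scores and a literal reading of Section 10.1.
- *Chance baseline imbalance biases the estimate.* A one-standard-error imbalance (0.354) would move the change-score difference by 0.354 × (1 − 0.7) = 0.11 at r = 0.7. That variation is already inside the change-score standard error; counting it again would double the loss.
- *The definitive trial will be sized on the wrong SD.* Section 10.1 says only that results may inform it. A residual SD can be computed later from the same data, and the change-score SD is the larger, so using it errs towards too many patients.
- *Sixteen cells for 60 people (3.75 each) show that the t-method fails.* That concerns the randomisation scheme, and the protocol gives no evidence of how much imbalance would remain.

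**Conclusion.** The point holds as a modest matter of precision and consistency. The protocol stratifies on "factors considered a priori to be prognostic of ELF", then fixes an analysis that leaves them out, sets the baseline slope at 1 for change outcomes, and does not name one analysed quantity throughout. If the factors are prognostic, as the protocol supposes, the unadjusted interval is generally too wide. By how much cannot be derived from the protocol.

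The gain from baseline adjustment rests on SD 1.12, 20 analysed per group, equal variances at baseline and follow-up, and an assumed r. It ranges from 0.72 to 0.63 at r = 0.5 down to about 1% at r = 0.9. The full model has a small downside when r is high and the factors turn out uninformative.

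**What to change.** In Sections 10.1 and 10.3.3, replace the t-method by a linear model of the week-48 and week-96 value on treatment, baseline value and the four stratification factors as main effects (not 16 cell indicators). State the same analysed quantity in both sections and apply the model to every continuous secondary outcome, including the questionnaires. Name the measurement that serves as baseline; for Fibroscan it is the screening one. For BMI, weight and waist, consider dropping the BMI ≥25 indicator where it duplicates the baseline value.

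Report the adjusted difference with its 95% interval and still no P-values, the residual SD alongside the raw SD for future planning, and the unadjusted difference as a sensitivity analysis.

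The cost is a wording change in two sections and five degrees of freedom. If none of the five covariates explained anything, the interval would be about 8% wider than the same t interval (1.5% for baseline alone). No new data are needed.

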### **Early termination visit**

Those individuals who withdraw from the study early will be requested to attend an early termination visit, during which the following assessments will be performed:

- history and examination
- adherence to maraviroc as assessed by (i) self reported adherence and (ii) pill counting by pharmacy/research team member.
- weight and BMI
- waist circumference
- liver function, renal function, CK, phosphate, fasting glucose, HbA1c and fasting lipid profile (blood draw)
- FBC (blood draw)
- HIV viral load (blood draw)
- ELF score (blood draw)
- Urine dipstick for macroanalysis and, for WOCBP, pregnancy testing
- CLDQ:NAFLD questionnaire
- SF-36 questionnaire

- WPAI-SHP questionnaire
- Dietary and exercise history
- Fibroscan

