### 10.3.2 Feasibility Outcome analyses

All analyses will be performed on available cases according to intention to treat (ITT) principles. Therefore, all individuals randomised within the study (including those subsequently withdrawn) will be included in outcome analyses.

The following analyses will be presented:

- a) Proportion of eligible individuals approached who are successfully recruited  
It is envisaged that a recruitment rate of at least 50% will be achieved. This takes into account the likelihood that a proportion of potential recruits will decline particularly owing to the requirement for twice daily pill taking.
- b) Monthly participant recruitment rate. This is expected to be a minimum of at least 2 participants consistently per month, with an average of 3-4.
- c) Participant retention in the study at 48 and 96 weeks in the maraviroc and non-maraviroc assigned groups. This is expected to be at least 65% (cf 35% discontinuation in the MOTIVATE study [9]).
- d) Proportion of participants for whom there is missing data at 48 and 96 weeks in the maraviroc and non-maraviroc assigned groups. This is expected to be less than 20% for all participants.
- e) Proportion of participants reporting adverse events at 48 and 96 weeks in the maraviroc and non-maraviroc assigned groups. This is expected to be less than 10% [18].
- f) Level of self-reported adherence to the study drug at 48 and 96 weeks in those allocated to the maraviroc group. This is expected to be greater than 90%.

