#### **10. 4 Procedure(s) to account for missing or spurious data**

In the event of missing data, only available data will be included in the analyses.

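### Viral suppression at weeks 48 and 96 uses available data only, so participants who leave after an observed rebound are not counted and suppression may be overstated

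*Protocol*

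**What the plan says.** Section 10.3.3 lists the percentage "with HIV viral load not detected (48 and 96 weeks" among the secondary outcomes, for which differences "will be presented exact 95% binomial confidence intervals". The missing-data rule in section 10.4 is general: "In the event of missing data, only available data will be included in the analyses". Section 10.3.2 says "All analyses will be performed on available cases according to intention to treat (ITT) principles" and draws from this that "all individuals randomised within the study (including those subsequently withdrawn) will be included in outcome analyses".

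Viral load is measured more often than it is reported. Table 1 and section 7.6 schedule it at weeks 24 and 72 as well as 48 and 96, and at week 4 in the maraviroc group. The early termination visit includes "HIV viral load (blood draw". Nothing says that any of these other results enters the week-48 or week-96 percentage.

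Section 10.1 plans "with 20 patients in each group for the analysis" and adds: "Assuming an attrition rate of 33%, a target of 30 individuals will be recruited per group". Section 8.11 makes withdrawal likely, at the investigator's discretion, when compliance with the study drug is below 80%.

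**The concern.** Section 6.1 requires at least six months of suppression below 50 copies/ml before entry, with one blip allowed. Suppression therefore starts at essentially 100%, and the information in this outcome lies in later detectable results. The trial can observe such a result at week 24, week 72 or early termination and still leave it out of the table, because the participant has no sample at the reported week.

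Two features make this more than a detail. First, the protocol plans for a third of each arm to be lost. Second, the compliance route to withdrawal exists only in the maraviroc arm, since only that arm takes study drug. If leavers rebound more often than stayers, the percentage is too high; if this differs by arm, the comparison is distorted as well. The outcome is the planned between-group check on HIV control after a drug is added to a suppressive regimen.

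**Working it through.** **Inputs.** 20 analysed and 30 recruited per group, 33% attrition (section 10.1); exact binomial intervals (section 10.3.3); available data only (section 10.4). The number of leavers with rebound, k, is not in the protocol and is varied from 0 to 10.

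**The plan's own figure.** 20 / (1 − 0.33) = 29.9, rounded up to 30, which reproduces the target. It implies 30 − 20 = 10 participants per arm without data.

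**Interval.** For x suppressed of n, the Clopper-Pearson 95% limits are the 0.025 quantile of Beta(x, n − x + 1) and the 0.975 quantile of Beta(x + 1, n − x). When x = n the lower limit is 0.025^(1/n); for n = 20 this is 0.832.

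**One arm, assuming that all 20 seen are suppressed.** The plan divides by those seen. The all-randomised figure is (30 − k)/30 when k leavers rebounded and the other leavers stayed suppressed.

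| Leavers with rebound (k) | As planned | All randomised |
|---|---|---|
| 0 | 20/20 = 100% (83.2 to 100) | 30/30 = 100% |
| 1 | 20/20 = 100% (83.2 to 100) | 29/30 = 96.7% (82.8 to 99.9) |
| 3 | 20/20 = 100% (83.2 to 100) | 27/30 = 90.0% (73.5 to 97.9) |
| 5 | 20/20 = 100% (83.2 to 100) | 25/30 = 83.3% (65.3 to 94.4) |
| 10 | 20/20 = 100% (83.2 to 100) | 20/30 = 66.7% (47.2 to 82.7) |

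The planned column does not move with k. The last row is also the figure with every missing value counted as not suppressed. The overstatement runs from 0 to 100 − 66.7 = 33.3 points.

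**Smaller loss.** Section 10.3.2(d) expects missing data in fewer than 20% of participants. At 20%, 0.20 × 30 = 6 are missing, and the range shrinks to 0 to 6/30 = 20 points.

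**Between arms (assumed counts).** With k = 3 in the maraviroc arm and k = 0 in the other, the plan shows 100% against 100%, a difference of 0. Over all randomised it is 90% against 100%, a difference of 10 points.

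**Rebound without leaving.** If 3 of the 20 who stay are detectable at the visit, the plan does show it: 17/20 = 85.0% (62.1 to 96.8).

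**The case against.** A reader might infer that this outcome cannot show loss of HIV control at all. The protocol does not support that. Anyone detectable at week 48 or 96 is counted, section 7.7 asks for every effort to keep people who stop study drug in follow-up, and rebound is not among the listed reasons for stopping study medication. Nor is it established that leavers rebound more often than stayers, so bias is possible rather than shown.

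It can be said that an early termination result is itself available data and that assigning such samples to time points belongs in the statistical analysis plan, which is not shown. That has some force, but the outcome is tied to weeks 48 and 96 and the missing-data rule is fixed in the protocol. An analysis plan that follows it inherits the gap. Section 10.3.2 may mean only that participants are analysed as allocated and that data from those who later withdraw are not discarded. As worded, however, it promises that everyone randomised is included, which available cases cannot deliver.

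Two objections to possible remedies stand. Adding only the detectable leavers as failures would give 20/23 = 87.0% (66.4 to 97.2) for k = 3, but it drops the 7 leavers whose last value was suppressed; using both kinds gives 27/30 = 90.0%. Counting missing as not suppressed largely reproduces retention, which is already a primary measure, and would score leavers who remain suppressed on background therapy as failures. A single last value of 50 or more may also be a blip of the kind that section 6.1 tolerates.

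**Conclusion.** The point holds as a risk of overstatement. The protocol fixes a rule under which a rebound seen before departure is not counted in the suppression percentage, and this is at odds with its statement that everyone randomised is included. With 10 of 30 lost per arm and all 20 seen suppressed, the overstatement is 0 to 33 points per arm; with 20% missing it is at most 20. Where the truth falls depends on the number of leavers with rebound, which is unknown. Distortion between arms needs the further assumption that this number differs by arm, for which the maraviroc-only compliance route gives a plausible but untested reason. This is one secondary outcome of a feasibility pilot, so the primary objectives are unaffected. It is still worth correcting before analysis.

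**What to change.** Keep the available-case percentage at weeks 48 and 96 and add two lines beside it, over all randomised and by arm:

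1. Where the scheduled sample is missing, use the last on-study viral load, including the early termination sample, symmetrically: 50 copies/ml or more is not suppressed, below 50 is suppressed. Label it a last observed value, and state how many participants have no sample after randomisation.
2. Count missing as not suppressed, labelled a conservative bound that also reflects retention.

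Reword section 10.3.2 so that it agrees with section 10.4, for example by saying that participants are analysed as allocated using the data available and that the viral suppression outcome is also shown over all randomised.

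The cost is two table lines from samples already scheduled, with no new visits. The reported suppression rate may look less favourable.

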#### **10. 4 Procedure(s) to account for missing or spurious data**

In the event of missing data, only available data will be included in the analyses.

### **11 DATA HANDLING**

#### **11.1 Data collection tools and source document identification**

An Electronic Data management system MACRO™ will be used in this study.

**All information will be recorded in source data and documentation that will be filed in patients' notes.**

A source data worksheet will be created to capture all the relevant information and will be filed as source documentation in the patient notes. A source data agreement will be completed prior to recruitment commencing to ensure all parties are aware which documents constitute source data.

Data from the source will be entered onto the electronic case report form (eCRF) on the Web-based MACRO™ electronic data capture system.

#### **11.2 Data handling and record keeping**

MACRO™ will be used for data entry. Data entered will be checked by the Data Manager in accordance with the Data Management Plan and queries raised to the clinical sites via MACRO when appropriate. Clinical sites will be responsible for the entry of data into the eCRF. Patient data will be entered using study number only and no patient identifiable data will be seen by the data management team. Analysis will be the responsibility of the CTU statisticians.

